#### Exercise activities

Each week, participants’ exercise and physical activity levels will be assessed. Participants in the exercise condition are requested to indicate their *compliance* to the guided and individual running sessions. Additionally, if applicable, they are asked to indicate whether they performed a missed guided running session on their own, and whether they performed this session according to the fixed running schedule or not. Besides that, they are requested to indicate if they performed *other exercise activities* than running during the past week (type, duration, and frequency). Participants in the control condition will be asked to indicate whether they engaged in exercise activities during the past week (type, duration, and frequency). Finally, all participants are requested to report their *physical activity* during the past week: ‘On how many days a week were you physically active during at least 30 min a day (only count physical activity that is equally demanding as brisk walking or biking. Activities shorter than ten minutes do not count) – during your work and free time together?’ (*0-7 days*) [77].

#### Subjective exercise experiences

To measure how participants in the exercise intervention experience the running sessions, we will administer single-item measures about *pleasure* and *effort.* The items are introduced as follows: “Can you indicate with a report mark between 1 (not at all applicable) to 10 (extremely applicable) how you experienced last week’s running sessions?” Separate ratings will be collected for the guided and individual running sessions. Additionally, the extent to which employees can ‘unwind’ from work during the running sessions will be measured using an adapted version of the 4-item *psychological detachment* scale of the Recovery Experience Questionnaire [78]. An example item is: ‘Last week, I forgot about work during the running sessions’. Previous research shows that psychometric properties are good [78].

### Statistical analyses

#### Sample size

Based on previous research, it is difficult to predict an exact effect size on which we can base our sample size, given that these studies report small to large effect sizes [19, 20, 22, 23], and that they differ in design (i.e., duration of exercise intervention; absence of control condition) and target audience (i.e., low to clinical levels of work-related fatigue). Since we conduct our study among employees with high but no clinical levels of work-related fatigue (we expect a decrease in work-related fatigue, but not as large as we would expect among employees with clinical levels) and our intervention is relatively short, we expect a small to medium effect size. To determine sample size, a power analysis has been conducted in the statistical program G*power [79]. This analysis was based on a repeated measures ANOVA with work-related fatigue as within subjects factors and condition as between subjects factor. This analysis showed that a total of 90 participants was required in order to detect a small to medium effect of .15 on the primary outcome work-related fatigue from pre to post intervention, given a two-sided 5 % significance level, a power of 80 %, and an correlation of .05 across repeated measures [80]. Because we anticipated a dropout rate of about 20 %, we intend to recruit 108 participants.

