### Analyses of primary and secondary outcomes

We will use intention-to-treat analysis, meaning that all participants who are randomized to a condition will be included in the analyses. To test the efficacy of the exercise intervention (i.e. change in primary and secondary outcomes from pre [T0] to post [T6]), we will perform 2x2 repeated measures (M)ANOVAs with condition (exercise versus wait list) as between-subjects factor, and time (pre [T0] versus post [T6]) as within-subjects factor. We will conduct a RM-MANOVA for the three indicators of work-related fatigue together (*Hypothesis 1*). Furthermore, we will conduct separate RM-(M)ANOVAs for respectively self-efficacy (*Hypothesis 2a and 2b*), sleep (*Hypothesis 2c and 2d*), work ability (*Hypothesis 2e*), cognitive functioning (*Hypothesis 2f*), and aerobic fitness (*Hypothesis 2 g*). The Matching Task will be analyzed using a 2x2x2 mixed design ANOVA, with ‘run type’ (switch versus repetition), and time (pre versus post) as within-subjects factors, and condition as between-subjects factor (exercise versus wait list). In all analyses, we are particularly interested in the ‘condition x time’ interaction, because this indicates that the conditions differ from each other with respect to the development of the outcome measure over time. If applicable, significant interactions will be further examined by paired-sample t-tests. Partial eta-squared will be reported as effect size.

Additionally, to obtain more thorough insight into the clinical meaningfulness of the changes brought about by the exercise intervention [81], we will perform a Chi-Square Test to see if the number of participants who score below cut-off scores of fatigue after the intervention period (T6) differs between the intervention and the control condition (emotional exhaustion <2.2 on the UBOS; overall fatigue: <22 on the FAS).

To investigate whether intervention-effects last during the follow-up period, for each primary and secondary outcome measure, a repeated measures MANOVA will be performed to see whether it differs between pre (T0), post (T6), 6 weeks after the intervention period (T7), and 12 weeks after the intervention period (T8). If the overall time effect of MANOVA is significant, post hoc tests will be carried out to exactly determine between what time points the outcome had changed. As follow-up measures are only available for the intervention condition, the control condition will not be included in these analyses.

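### The stated 80% power with 90 participants needs a correlation of .50 rather than the printed .05, refers to a 0.60 SD between-arm difference in change, and is not the power of the planned primary test

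*Protocol article*

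**What the plan says.** The Sample size section of the protocol article argues for a modest effect because the sample is non-clinical and the programme is short: "we expect a small to medium effect size". It then gives the requirement: "a total of 90 participants was required in order to detect a small to medium effect of .15 on the primary outcome work-related fatigue". The power is 80%, and the remaining inputs are "given a two-sided 5 % significance level" and "an correlation of .05 across repeated measures". The model is described as follows: "This analysis was based on a repeated measures ANOVA with work-related fatigue as within subjects factors and condition as between subjects factor". The metric of .15 is not named, and no target difference is given in SD units or scale points.

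Under Analyses of primary and secondary outcomes, the contrast of interest is the condition by time interaction over T0 and T6. Hypothesis 1 is tested jointly: "We will conduct a RM-MANOVA for the three indicators of work-related fatigue together".

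**The concern.** Three things do not fit together. The printed inputs may not give 90. An interaction f is not on the same scale as a standardised mean difference, so calling .15 small to medium may suggest more sensitivity to modest between-arm differences than the trial has. And the power analysis concerns one variable, whereas the primary test concerns three. At stake is what the 80% refers to. Someone who takes it as 80% power for a small to medium difference between arms could read a null result as evidence against such a difference.

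**Working it through.** **Inputs.** From the Sample size section: effect .15, alpha .05 two-sided, power 80%, correlation rho = .05 as printed, N = 90. From Randomization and blinding: 1:1 allocation. From the analysis section: k = 2 arms, m = 2 time points, interaction as the effect of interest. Assumed here: .15 is Cohen's f as G*Power defines it; 90 participants are analysed; the variance is the same at both time points.

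**1. Reproducing 90.** For the within-between interaction, lambda = f² × N × m / (1 − rho), with df 1 and N − 2.

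- rho = .50: lambda = .0225 × 90 × 2 / .50 = 8.1, power 80.4%. The smallest even N reaching 80% is 90, so the figure reproduces exactly.
- rho = .05: lambda = .0225 × 90 × 2 / .95 = 4.26, power 53.3%. The N required is 168.

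Other readings with f = .15 do not give 90. The between-subjects test needs 186 (rho .05) or 264 (rho .50). The SPSS-type f convention needs 352 to 354. Three time points need 138 or 74, and four need 118 or 62. Six time points at rho .05 come close, at 92, but the test has two. With k = m = 2 the main effect of time gives the same N as the interaction, but the analysis section makes the interaction the effect of interest.

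**2. What f = .15 means here.** In a 2x2 layout the four cell deviations for the interaction are +a or −a, and f = a/SD. The between-arm difference in change is 4a, so 4 × .15 = 0.60 SD of the raw score, whatever rho is. Cross-check by the two-sample route: lambda = d² × (N/4) / [2(1 − rho)] = .36 × 22.5 / 1 = 8.1 at rho .50, the same value as in step 1.

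**3. Power at N = 90 for other differences d.** Put f = d/4 into the formula of step 1.

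| d (SD) | rho .05 | rho .50 | rho .70 |
|---|---|---|---|
| 0.2 | 10% | 16% | 23% |
| 0.3 | 17.5% | 29% | 44% |
| 0.4 | 28% | 47% | 68% |
| 0.5 | 40% | 65% | 86% |
| 0.6 | 53% | 80% | 95% |

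Simulation agrees at rho .50 (79.4% for 0.6 SD, 29.2% for 0.3 SD) and at rho .05 (53.1% and 17.0%).

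**4. Power of the planned primary test.** With three change scores, the RM-MANOVA interaction is a Hotelling test with df 3 and 86. If all three indicators shift by 0.60 SD, rho is .50 and the changes have common correlation r, then lambda = 8.1 × 3 / (1 + 2r).

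| r | lambda | power |
|---|---|---|
| .3 | 15.2 | 91% |
| .5 | 12.2 | 83% |
| .6 | 11.0 | 79% |
| .7 | 10.1 | 75% |
| .8 | 9.3 | 71% |

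If only one indicator shifts by 0.60 SD and the changes are uncorrelated, lambda stays at 8.1 and power is 64%. The article gives no value for r.

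**The case against.** The label is not wrong on its own scale: .15 lies between the conventional small (.10) and medium (.25) values of f. That stands. The fault lies in the unnamed metric and the missing translation into a between-arm difference.

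The .50 is an inference. It makes a misprint of .05 likely but does not prove one, and any power figure below 80% must be quoted with its correlation. A reader might conclude that power for a realistic effect is simply 29%. The article does not support that as an unconditional figure: 0.3 SD appears nowhere in it, and the same difference has 17.5% power at rho .05 and 44% at rho .70. At rho .70 even 0.5 SD reaches 86%.

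A reader might also infer that the trial is sized only for a large effect. That is too strong: 0.60 SD is slightly above a conventional medium d, and 0.5 SD still has 65% power at rho .50.

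Nor does the change of test show a loss of power. With all three indicators shifting, the range of 71% to 91% straddles 80%, and the direction depends on correlations that the article does not give.

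Finally, the plan to report partial eta-squared is not an error, since nothing equates it with .15. Expressing the result in baseline SD units would be a doubtful remedy: two of the three indicators have entry cut-offs, which restrict their spread at T0.

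**Conclusion.** The point holds in this form. The stated inputs do not give 90; at the printed correlation, power is 53% and 168 participants would be needed. With .15 read as interaction f and a correlation of .50, 90 is exact, and the 80% then belongs to a 0.60 SD between-arm difference in change. At that correlation, differences of 0.2 to 0.5 SD have 16% to 65% power. The 80% is also not the power of the Hypothesis 1 test, which is about 64% to 91% over the scenarios shown. This rests on the f reading, 90 analysed participants, equal variances and, for the RM-MANOVA, assumed correlations among the changes. It is a matter of how the sample size is stated and interpreted; the design itself is not shown to be invalid.

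**What to change.** In the Sample size section:

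- Correct the correlation of .05, or justify it and revise N or power to match.
- Name .15 as the G*Power interaction f for two arms and two time points, and state that it equals a 0.60 SD between-arm difference in change.
- Give power at 90 analysed participants for 0.3, 0.4 and 0.5 SD, with the correlation assumed.
- Give power for the three-indicator RM-MANOVA over a range of correlations among the indicators, including the case where only one shifts.
- State that a null result will not be read as excluding a small to medium between-arm difference.

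The cost is a less favourable statement of the trial's sensitivity. No extra enrolment or change to the analysis is required.

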### Randomization and blinding

Participants will be randomly assigned to either an exercise condition or a wait list condition at a 1:1 ratio. Because the intention is to conduct the exercise intervention in groups of 10 participants, randomization will be based on a block size of 20. When the number of 20 eligible participants in a block is reached, participants in the exercise intervention condition start the intervention and the participants in the wait list condition remain on the wait list. The randomization procedure will be carried out after the participant has completed the baseline measurement (T0). The randomization procedure will be executed by the first author ([name]) or research assistant, using sealed opaque envelopes. The participant opens the envelope and tells the researcher to which condition (s)he has been assigned.

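### The printed sample-size inputs do not give 90: a pre-post correlation of .05 needs 168 participants and leaves 53% power at 90, while .50 gives 90 exactly

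*Protocol article*

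**What the plan says.** The Sample size section of the protocol article describes the calculation this way: "This analysis was based on a repeated measures ANOVA with work-related fatigue as within subjects factors and condition as between subjects factor". It reports that "a total of 90 participants was required in order to detect a small to medium effect of .15 on the primary outcome work-related fatigue", with the effect measured from before to after the intervention. The remaining inputs are 80% power, "given a two-sided 5 % significance level" and "an correlation of .05 across repeated measures". The target is then raised to 108 for dropout.

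The section on analyses of primary and secondary outcomes sets out the matching model. It has condition as the between-subjects factor and "time (pre [T0] versus post [T6]) as within-subjects factor". On the effect to be tested it says: "we are particularly interested in the ‘condition x time’ interaction". The Randomization and blinding section gives 1:1 allocation. No other section states a correlation between the repeated measurements.

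**The concern.** In a two-occasion design analysed through the condition by time interaction, the required sample size is nearly proportional to one minus the pre-post correlation. With a correlation close to zero, the baseline measurement adds noise to the change score instead of removing it. A value of .05 is thus an unfavourable input, and it is hard to square with a requirement as low as 90 for an effect of .15.

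What is at stake is the 80% power claim for the primary outcome. If the printed correlation is what was assumed, the trial has little better than an even chance of detecting its target effect. If it is a misprint, the sample size stands and only the report is wrong. The article does not let a reader decide between the two. A later trial that copied the printed inputs would also get a very different sample size from the one reported here.

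**Working it through.** **Inputs**

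- Two-sided alpha .05, power 80%, effect .15, correlation .05, stated result 90: Sample size section.
- Two groups, 1:1: Randomization and blinding section.
- Two measurements (T0 and T6), condition by time interaction: section on analyses of primary and secondary outcomes.
- Assumption: .15 is Cohen's f, the metric G*Power uses for repeated measures ANOVA.

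**Formula.** For the within-between interaction with k = 2 groups and m = 2 measurements, the test is a noncentral F with

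lambda = f² × N × m / (1 − rho), df1 = (k − 1)(m − 1) = 1, df2 = (N − k)(m − 1) = N − 2.

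Here f² = .15² = .0225.

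**Printed inputs, rho = .05**

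- N = 90: lambda = .0225 × 90 × 2 / .95 = 4.05 / .95 = 4.26. The critical F(1, 88) is 3.95, and power is 53.3%.
- N = 108 (everyone recruited completes): power is 61.1%.
- The smallest N with equal groups and at least 80% power is 168: lambda = .0225 × 168 × 2 / .95 = 7.96, power 80.1%.

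**Reproducing 90.** With rho = .50, lambda = 4.05 / .50 = 8.10. Power at 90 is 80.4%, against 79.5% at 88, so the smallest N with equal groups is 90. Scanning rho from 0 to .60 in steps of .01, the required N falls within 2 of 90 only at .49 (92), .50 (90) and .51 (88).

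**Cross-checks**

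- An f of .15 in this layout is a between-arm difference in change of 4 × .15 = 0.6 SD, and the SD of change is √(2(1 − rho)). A normal approximation on change scores then gives N = 166 at rho = .05 and N = 88 at rho = .50, in line with the F results.
- Simulating the interaction test at N = 90 gave 53.8% power at rho = .05 and 80.6% at rho = .50.

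**Other readings at rho = .05, two measurements**

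| Reading | Required N |
|---|---|
| Test of the between-subjects factor | 186 |
| One-sided equivalent (alpha .10) | 132 |
| .15 as f² | 28 |
| .15 as eta² | 24 |
| .15 as d (f = .075) | 666 |

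None is near 90. An f defined without the correlation gives 352. Six measurements at rho = .05 would need 92, but the article powers a change between two occasions and specifies a 2 × 2 model.

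**Sensitivity to the correlation, f held at .15**

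| rho | Power at N = 90 | N for 80% power |
|---|---|---|
| .05 | 53% | 168 |
| .30 | 66% | 126 |
| .40 | 73% | 108 |
| .50 | 80% | 90 |
| .60 | 88% | 72 |

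**The case against.** The strongest reply is that this is a misplaced digit. The 90 was program output, it reproduces exactly at .50, and a reporting slip is much likelier than a wrong calculation. On that reading the 90, the recruitment target and the 80% are untouched, and leading with 168 participants overstates the problem. Much of this stands: the misprint is the most plausible explanation, and the finding is a false input, not proof of an underpowered trial. But the article itself cannot settle the matter, and the two possibilities are far apart.

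Three narrower objections also have weight.

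- The metric of .15 is not named. Cohen's f is an assumption here, although the other metrics tried do not give 90 at .05 either.
- Entry requires high scores on two of the three fatigue measures. One can argue that this restriction of range lowers the pre-post correlation, so that even .50 is optimistic. Restriction also shrinks the baseline SD, however, so for a fixed raw effect power need not fall. The article gives no SDs or correlations to decide this, and the conclusion does not rely on it.
- Hypothesis 1 is to be tested by a repeated measures MANOVA on three indicators, whereas the power calculation is for a repeated measures ANOVA. The figures above check the calculation as reported. They are not the power of the multivariate test.

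**Conclusion.** The concern holds. For the two-measurement, two-arm design that the article states, and with .15 read as Cohen's f, the printed correlation of .05 is incompatible with a requirement of 90. It implies 168 participants for 80% power, or 53% power at 90. A correlation of .50 gives 90 exactly. Either the correlation is misprinted by a factor of ten or the sample size is wrong. The exact match favours a misprint but does not establish it. Because the figure supports the power claim for the primary outcome, it must be corrected or explained.

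**What to change.** Check the saved G*Power output and state the correlation that was entered, together with the effect-size metric and the test option chosen.

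- If the value was .50, correct the figure and add one sentence on sensitivity: at 90 completers and f = .15, power is 66%, 73%, 80% and 88% for correlations of .30, .40, .50 and .60.
- If .05 was really intended, restate the power at 90 completers as about 53%. An analysis of T6 adjusted for baseline would restore about 80% at 90 for the same 0.6 SD difference. With rho = .05, lambda = (90 / 4) × .36 / (1 − .05²) = 8.12, and power is 80.5%. That change of model is a separate decision.

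Neither route requires extra enrolment. The cost is one corrected figure and one sentence, and possibly a stated power that looks less favourable.

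### The target of 108 allows for 16.7% loss, not the stated 20%, so about 86 rather than 90 remain and power falls slightly short of 80% (minor)

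*Protocol article*

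**What the plan says.** The Sample size section (protocol article, Statistical analyses) reports that "a total of 90 participants was required in order to detect a small to medium effect of .15", "given a two-sided 5 % significance level, a power of 80" per cent, and "an correlation of .05 across repeated measures". It then moves from the required number to the recruitment target: "Because we anticipated a dropout rate of about 20" per cent, "we intend to recruit 108 participants". The Abstract repeats N = 108.

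The Randomization and blinding section says that "randomization will be based on a block size of 20", chosen because the exercise groups are meant to have ten members. It ties the start of the intervention to a full block: "When the number of 20 eligible participants in a block is reached, participants in the exercise intervention condition start the intervention". Each participant is randomised individually, by envelope, after the baseline measurement.

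**The concern.** The 90 is what the power calculation requires. The recruitment target should therefore be large enough that 90 remain after the anticipated loss. 108 looks like 90 with 20% added on top, and that does not leave 90 when 20% of those recruited drop out. If so, the trial does not have its stated 80% power at its own dropout rate.

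The target also sits awkwardly with the block scheme. If the intervention starts only when a block reaches 20, a target that is not a multiple of 20 leaves the last block short of its trigger.

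**Working it through.** **Inputs.** From the Sample size section: 90 required, effect .15, two-sided 5%, power 80%, correlation printed as .05, dropout about 20%, target 108. From Randomization and blinding: 1:1 allocation, block size 20. Reading the .15 as Cohen's f is an assumption; the article names G*Power and a repeated measures ANOVA but not the effect-size metric.

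**1. How 108 arises.** 90 x (1 + 0.20) = 108 exactly.

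**2. What 20% loss requires.** N/(1 - d) = 90/0.80 = 112.5, so 113, or 114 for equal arms.

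**3. What 108 delivers.** 108 x 0.80 = 86.4, so about 86, which is 4 short of 90. The loss that 108 can absorb is 1 - 90/108 = 18/108 = 16.7%.

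**4. Reproducing the 90.** For the condition-by-time interaction with two groups and two time points, the noncentrality parameter is λ = f² x N x 2/(1 - ρ), with 1 and N - 2 degrees of freedom.

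- ρ = .5, N = 90: λ = 0.0225 x 180/0.5 = 8.10, power 80.4%. This is the smallest even N that reaches 80%, so the stated 90 is reproduced.
- ρ = .05 (as printed), N = 90: λ = 0.0225 x 180/0.95 = 4.26, power 53%. Reaching 80% would take 168.

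Other readings do not rescue the printed .05. The between-subjects form gives 186 with ρ = .05 and 264 with ρ = .5. Doubling alpha to 0.10 with ρ = .05 gives 132. None gives 90.

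**5. Power at 86.**

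| Correlation | λ at N = 86 | Power at 90 | Power at 86 |
|---|---|---|---|
| .5 (reproduces the 90) | 0.0225 x 172/0.5 = 7.74 | 80.4% | 78.5% |
| .05 (as printed) | 0.0225 x 172/0.95 = 4.07 | 53% | 51% |

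A check that uses no correlation takes 80% at 90 as given and scales by the normal approximation: (1.96 + 0.84) x √(86/90) - 1.96 = 0.78, which is a power of 78.2%. The shortfall is thus about 2 points whenever the 90/80% pairing is accepted.

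**6. Blocks.** 108 = 5 x 20 + 8. Five full blocks hold 100 and six hold 120. With 20% loss and ρ = .5, these leave 80 and 96 participants, with power 75.5% and 82.9%.

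**The case against.** **The shortfall is small and the dropout approximate.** On the correlation that reproduces the 90, the gap is five recruits (six for equal arms) and under 2 points of power. The article says about 20%, admits that the effect size is hard to predict, and does not say whether the 20% applies at T6 or includes the later follow-ups. If loss at T6 is no more than 16.7%, 90 do remain. All of this bears on severity, and it stands. It does not remove the error, because the exact factor of 1.20 shows that 20% was the figure applied.

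**Intention to treat.** The analysis section includes everyone randomised, so one might say that dropout costs nothing. But the planned 2x2 repeated measures analysis needs both T0 and T6, and the sample size section itself adds participants for dropout. The 86 does assume complete cases, with no imputation.

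**Stronger readings that the article does not support.**

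- A reader might quote 78% without conditions. It holds only if 90 with 80% power is accepted, which needs a correlation other than the printed one.
- A reader might infer that a baseline-adjusted analysis makes up the difference and settles the matter. With 86 completers it gives about 89% at a correlation of .5 but 78.6% at the printed .05, and it is not the planned analysis.
- A reader might infer that the last eight participants cannot be randomised, or that the trial must end at 100 or 120. Neither follows. Each person is randomised at the baseline appointment, and an incomplete last block is ordinary. Drawing eight from a block of ten and ten gives a split of 5:3 or closer in 83% of cases. Groups of ten are described in that section as an intention. What remains is an operational gap about when a short last group starts, which the full protocol may cover.

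**Conclusion.** The point holds as a minor error. The step from 90 to 108 is wrong as written: 20% loss needs 113 (114 for equal arms), and 108 leaves about 86 with both measurements and covers 16.7% loss. Power at the stated dropout is about 78% rather than 80%, given complete-case analysis at T6, f = .15 and the correlation of .5 that reproduces the 90.

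The printed correlation of .05 is a separate and larger discrepancy in the same section. Under it power would be about 51% at 86 and 53% at 90, so no restated power figure is safe until it is resolved.

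The mismatch between 108 and the block size of 20 is real, but secondary and operational. It does not threaten the validity of the randomisation.

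**What to change.** First reconcile the printed correlation with the 90, since every power figure depends on it.

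Then correct the dropout sentence in one of two ways:

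- State that 108 allows for 16.7% loss.
- Keep 20% and restate the power as about 78% with 86 completers, naming the correlation used (.5, if that is confirmed).

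If the sponsor prefers to keep both 80% power and 20% dropout, the target becomes 113 (114 for equal arms), and N in the Abstract changes with it.

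Separately, reconcile the target with the block-based start rule. Either say how a last block that stays below 20 is handled, or give a target that is a multiple of 20 with the power for that number. Any change should stay consistent with the group size given under Exercise intervention condition.

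The first two options cost a sentence and a slightly less favourable stated figure. The third costs five or six more recruits. The block point costs one sentence, or a changed target if that route is chosen.
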